### Strategies to improve adherence to interventions {11c}

Participant medication adherence plans will not be necessary as treatment dosing will occur on-site and under the supervision of study personnel responsible for participant care and monitoring. However, participants will be strongly encouraged to speak to the study staff and/or Qualified Investigator should they have any questions or concerns about the study procedures involved.

### Relevant concomitant care permitted or prohibited during the trial {11d}

Concomitant standard-of-care psychiatric interventions and medications that participants would normally receive from their primary care provider/psychiatrist must be discontinued, as described in the study eligibility criteria. To ensure safety and to mitigate any associated risks or adverse effects, participants will follow our antidepressant medication tapering and washout protocol before they begin the study. In alignment with the Human Hallucinogen Research Safety guidelines, any potential adverse events will be mitigated through cultivation of a positive interpersonal atmosphere between the study staff and participants [28]. During the study treatment, and after the MRI scans, supportive psychotherapy will be used to guide and facilitate a calm affect, during a participant’s psychedelic experience, also acting as a de-escalatory method in response to any panic or aggressive behaviour. Although it is highly improbable [16, 21, 81], in the event that a participant experiences moderate agitation and does not respond to the psychological support provided by study staff session, the Qualified Investigator will be notified and authorize the administration of an oral sedative medication, such as sublingual 1 mg lorazepam tablet (considered a rescue medication).

### Provisions for post-trial care {30}

Follow-up assessments will be required after each treatment visit to provide additional psychotherapeutic support and to allow for participant reflection. Participants who have discontinued or completed their participation in the trial will be permitted to resume their usual standard-of-care for their depression symptoms. Participants will be advised in the informed consent that they will need completed paperwork by their general practitioner or psychiatrist to apply to Health Canada’s Special Access Program for compassionate care if they express interest in continuing psilocybin treatment for their depression symptoms beyond the study’s duration. They will also be informed that neither granted access nor affordability can be guaranteed if they pursue this option.

### Outcomes {12}

Exploratory imaging analysis will consist of voxel-wise analyses to fully characterize regional group and session effects. These analyses will probe circuit-based perspectives by considering the following four relevant resting-state networks: (1) salience, (2) left frontoparietal, (3) right frontoparietal, (4) default mode brain regions. Furthermore, we will conduct brain and behavioural responses, namely regional CBF changes in relation to the MADRS scores. Well-validated markers of brain neuroplasticity (BDNF), systemic inflammation (CRP), and glial pathology (S100B) will be measured in blood at baseline and subsequently evaluated as predictors of treatment response.

### Participant timeline {13}

The trial schedule is outlined in Figs. 1 and 2, illustrating the timeline from eligibility screening to final follow-up that includes time points for each treatment visit and follow-up, the clinical scales used, as well as the timing of our primary and secondary outcomes. See participant timeline below for details.

**Fig. 2 Fig2:**
[figure not shown]
Schedule of events

A week into each participant’s washout period, a baseline assessment (day 7) will be conducted, which will include clinical scales, a baseline MRI, and an optional blood biomarker collection, if the participant has indicated their agreement to provide this on the written consent form. One week (day 14) after baseline is the first treatment visit where clinical questionnaires will be completed. Afterwards, participants will be administered either 25 mg of psilocybin or MCC placebo depending on their randomized group allocation. Over the course of 8 h post-psilocybin intake, participants will be monitored every 30 min for routine vitals (HR, BP, %SPO_2_) and dissociative symptoms, using the 6-Item Clinician Administered Dissociative Symptoms Scale and mental status examination by the study coordinator. Approximately 1 h after dosing, participants will undergo a second MRI scan that will include a T1-weighted anatomical scan, ASL and resting-state fMRI sequence with the total scan time lasting approximately 1 h. Participants will then be brought by study personnel to a comfortable room where supportive psychotherapy will be provided. An ECG will be performed within 48 h after treatment administration on the first treatment day. All participants will have a follow-up visit 1 day after the initial treatment that includes relevant clinical scales, psychotherapeutic support, and participant reflection. A second follow-up visit 1 week after the first treatment visit will be remote and will include relevant clinical scales, psychotherapeutic support, and participant reflection. Participants will return to the hospital for open-label treatment with psilocybin 25 mg on the second treatment visit. The QI or delegate will be in-house and available on-call during this time to manage any emergency situations should they arise. Supportive psychotherapy will be provided by a study psychotherapist during each participant’s psilocybin or placebo treatment. Prior to participant discharge, a risk assessment will be performed to ensure that they are safe to leave the center (e.g., risk of harm to self or others and likely serious physical impairment due to their mental state). If they are not deemed safe to leave by study personnel, the QI or delegate will be promptly notified, and the participant will be offered additional time for recovery. If the time exceeds the normal working day, the study QI/delegate will remain available to monitor the participant until the participant’s risk level is reduced and is suitable for discharge home or, if necessary, bring the participant to the emergency department and/or admit directly to the psychiatric unit for further emergency psychiatric care and stabilization.

### Sample size {14}

As this study will employ a longitudinal design with multiple visits where CBF measurements in individual subjects may reasonably be expected to be highly dependent across visits, we will model use linear mixed-effects models of CBF at all visits to account for effects of psilocybin and MCC placebo independently of baseline CBF. Specifically, we will use the following model (in *lme4* syntax):1$$CBF\sim Age+Sex+Drug+Drug\;x\;Visit+(\mathit1\;\vert\;ID)$$

To assess the difference in CBF associated with psilocybin relative to placebo, marginal means of a Visit x Drug interaction will be calculated using the *emmeans* package in R, and contrasts between baseline and treatment visit 1 CBF under psilocybin and placebo conditions will be calculated separately, and an additional contrast composed of the difference of these two contrasts will be calculated. Sidak’s correction for multiple comparisons will be used to adjust *p* values. The primary endpoint will be the contrast estimating the between-group difference in within-subject differences in psilocybin- and placebo-induced CBF changes at treatment visit 1 vs baseline (i.e. [V1 psilocybin − V0] − [V1 placebo − V0]).

As a power analysis, we simulate 500 datasets each for groups of size *N* = 5 − 50, in increments of 5. For each simulated subject, baseline CBF is sampled from a normal distribution 55 ± 13 mL/100/g min. At each subsequent visit, a ± 3% test-retest variability is added to the baseline CBF. At psilocybin visits, relative to subject-specific baseline CBF, a proportional 23% ± 23% increase in CBF is added. MCC placebo has no direct psychotropic effects. For each of these 500 datasets, a model (Eq. 1) is fit to the data, and the contrasts described above are calculated. Sufficient power is achieved when evaluation of the between-group contrast of interest for a given group size produce corrected *p*-values below *α* = 0.05 at a frequency equal to or greater than a pre-specified power of 80%. This power analysis suggests two groups of *N* = 20 are sufficient to reject the null hypothesis in > 80% of cases. Sensitivity analyses additionally suggest that sufficient power can be achieved with *N* = 25 in each group if test-retest variability is as high as 7.5%, or if psilocybin effect size and variance is scaled from 23% to as low as 15% [see Additional file 3]. As these simulated datasets are likely somewhat idealized relative to real-world data, we will use a total of *N* = 50 subjects with 25 allocated to each arm.

These anticipated CBF group session differences are consistent with a recently conducted acute neuroimaging clinical trial in bipolar depression [82]. Although we do not conduct a power analysis for H_A,2_, we provide context from the literature in support of the MADRS outcome measure. Example studies incorporating the MADRS outcome measure are provided [see Additional file 4], showing trial design, sample sizes, intervention details, and the reported changes in MADRS score [83–87].

Thus, our MADRS assessments for *N* = 50 is consistent with previous depression trials and support our second hypothesis (H_A.2_).

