### Trial design {8}

EMBRACE is a randomized, placebo-controlled, delayed-start trial that investigates neuroimaging, blood biomarkers, and clinical changes associated with psilocybin therapy in those with a unipolar depressive disorder. The protocol is documented as adhering to the SPIRIT checklist [see Additional file 1]. For the purposes of this study, a depressive disorder will include MDD or persistent depressive disorder (PDD) as indicated by the Mini-International Neuropsychiatric Interview (MINI) with a current major depressive episode as defined by the DSM-5.0 and confirmed by an interventional psychiatrist [75]. Study assessments/visits will occur at intervals that are reported in Fig. 2. This study aims to recruit and treat up to 50 participants at Sunnybrook Health Sciences Centre, University of Toronto, Toronto, Ontario, Canada. Participants will be screened by a study coordinator to determine study eligibility, and if eligible will undergo a baseline assessment, preparatory supportive psychotherapy, and neuroimaging 1 week prior to randomization. At the first treatment session (Treatment Visit 1), participants will be randomized to either group 1 or group 2. Participants in group 1 will receive a high dose of synthetic psilocybin (25 mg) while in group 2 will receive inert placebo (25 mg MCC). Three weeks later (Treatment Visit 2), participants in group 1 and group 2 will both receive a high dose of synthetic psilocybin (25 mg). This delayed-start design allows for the comparison of outcomes between the two groups while also evaluating the effect of the intervention over time. At each Treatment Visit, all participants will undergo neuroimaging after dosing, and two qualified staff members will observe and provide supportive psychotherapeutic support for approximately 8 h post-treatment administration. A diagram of the study design and stages is presented in Fig. 1.

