## Limitations of the trial design

Anticipated limitations of our trial design include its single-center design and modest sample size, potentially limiting generalizability. To enhance statistical power, we have incorporated three imaging time points to improve our ability to detect intra-subject changes and focused our primary neuroimaging analysis on a priori brain regions linked to MDD and psilocybin’s effects.

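### Eq. 1 pools psilocybin-visit variance from treatment visit 2 into the primary baseline-to-visit-1 CBF contrast, so its standard error is up to about 1.4 times too large and the within-arm standard errors are also wrong

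*Protocol article*

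**What the plan says.** Sample size {14} sets the model (Eq. 1): CBF on age, sex, drug and drug by visit, with a random intercept per participant. The text reads "we will model use linear mixed-effects models of CBF at all visits". In lme4 this specification implies one residual variance and equal covariance across visits and arms.

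The primary endpoint is "the contrast estimating the between-group difference in within-subject differences in psilocybin- and placebo-induced CBF changes at treatment visit 1 vs baseline", so only baseline (V0) and treatment visit 1 (V1) enter it. The two within-arm changes are also to be calculated, with Sidak adjustment.

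The power simulation draws baseline CBF as 55 ± 13. At later visits a ±3% "test-retest variability is added to the baseline CBF". At psilocybin visits a proportional 23% ± 23% "increase in CBF is added. MCC placebo has no direct psychotropic effects".

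Trial design {8} gives psilocybin to both arms at treatment visit 2 (V2). The Limitations section states "we have incorporated three imaging time points to improve our ability to detect intra-subject changes". Statistical methods {20a} repeats Eq. 1; its model selection adds only fixed-effect interactions (age, sex, prior failed treatments).

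On sensitivity, the plan reports that 25 per group also suffice at 7.5% test-retest variability, "or if psilocybin effect size and variance is scaled from 23% to as low as 15" percent.

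**The concern.** The stated assumptions contradict the equal-variance model that is fitted to them. Three of the four post-baseline arm-by-visit cells carry the large drug variance; the placebo V1 cell does not. With V0 and V1 alone and equal arms, a pooled residual averages the two arms correctly for the between-arm contrast. Adding V2 raises that residual, while the contrast estimate remains the difference in mean V1−V0 change. The third imaging visit can then reduce precision for the primary contrast, although the Limitations section presents it as a gain in power. At stake are the confidence interval of the primary endpoint in a 50-participant mechanistic trial and both within-arm intervals.

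Separately, the 15% sensitivity case can be read as robustness to a smaller effect. It scales mean and SD together.

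**Working it through.** **Inputs (Sample size {14}; Trial design {8}).** Baseline b: mean 55, SD 13, taken without measurement noise, as the simulation describes. Test-retest SD 3% of b. Drug effect: mean 23%, SD 23% of b. Placebo effect zero. n = 25 per arm, three visits. Assumptions: Drug identifies the arm; two-sided Sidak over the three listed contrasts (per-test alpha 1 − 0.95^(1/3) = 0.01695). The correlation of a participant's drug response between V1 and V2 is not given, so both extremes are shown.

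**The plan's own figure.** Simulated Eq. 1 power at 15 and 20 per arm:
- Same response at both visits, Sidak over 3: 0.785 and 0.911.
- Independent responses, Sidak over 2: 0.664 and 0.838.
- Independent responses, unadjusted: 0.795 and 0.919.

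Each reproduces 20 per group as the first grid size above 80%. Independent responses with Sidak over 3 give 0.779 at 20, just short.

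**True SE of the primary contrast.** E[b²] = 55² + 13² = 3194.
- Placebo Var(V1−V0) = 0.03² × 3194 = 2.87.
- Psilocybin Var(V1−V0) = 0.23² × 169 + 0.23² × 3194 + 2.87 = 8.94 + 168.96 + 2.87 = 180.8 (rounded).
- SE = √((180.8 + 2.87)/25) = 2.71.

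**SE reported by Eq. 1.** For balanced data the within-subject variance s² is the sum of the three pairwise-difference variances divided by 6, averaged over arms. The contrast SE is √(4s²/n).
- Placebo-first arm: 2.87 + 180.8 + 183.65 = 367.3.
- Psilocybin arm, independent responses: 180.8 + 180.8 + 343.7 = 705.2 (rounded).
- Psilocybin arm, same response: 180.8 + 180.8 + 5.75 = 367.3.
- Independent: s² = (705.2 + 367.3)/12 = 89.4; SE = 3.78; ratio 1.40.
- Same response: s² = (367.3 + 367.3)/12 = 61.2; SE = 3.13; ratio 1.15.

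With V0 and V1 only, s² = (180.8 + 2.87)/4 = 45.9; SE = 2.71; ratio 1.00.

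If Drug is coded as time-varying with one pooled baseline cell, simulation gives a ratio of about 1.0 (independent) to 1.3 (same response).

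**Power at 25 per arm (Sidak over 3).** Eq. 1: 0.896 (independent) to 0.969 (same response). Welch test on V1−V0: about 0.98.

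**Within-arm SEs, √(2s²/n).** Eq. 1 gives 2.67 (independent) or 2.21 (same response) for either arm.
- Placebo, true: √(2.87/25) = 0.34.
- Psilocybin, true: √(180.8/25) = 2.69. With the same response, Eq. 1 is about 18% too small (2.21/2.69 = 0.82); with independent responses it is about right.
- With V0 and V1 only but pooled variance: √(2 × 45.9/25) = 1.92 for both arms, so both remain wrong.

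**The 15% case.** 15%/15% = 23%/23% = 1.0, so the standardised effect does not change and Eq. 1 power stays at 89 to 96%. With mean 15% and SD held at 23%, Sidak power at 25 per arm is about 39 to 62% with Eq. 1 and about 71% with arm-specific variances.

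**The case against.** The strongest reply is that the error in the primary contrast is conservative and already priced in: the power simulation fits Eq. 1 itself, and 25 per arm exceeds 80% at both extremes. That stands. A reader might infer that the trial is underpowered or prone to false positives on its primary endpoint; under the base assumptions neither follows.

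The size depends on two things the article does not give: the V1/V2 response correlation and the coding of Drug. That stands too, and only a range can be stated. The separately calculated baseline-to-V1 contrasts under each condition suggest arm coding, without settling it.

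A reader might also infer that the test always runs far below 5%. Rejection of about 0.7% (independent) to 2–3% (same response) needs a null with zero mean effect but a 23% SD. With no drug effect at all, the simulated rate is 2.6% with a noise-free baseline and 4.9% with equal noise at baseline.

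Nor is the placebo interval shown to be useless. The plan calls its simulated data somewhat idealised, and the Background cites a minimal detectable change of about 10 mL/100 g/min. If that is a 95% limit (an assumption), the retest SD is 10/(1.96 × √2) = 3.6 mL, or 6.6% of 55. With that noise at every visit, the true placebo SE is about 1.05, Eq. 1 overstates it 2.3 to 2.7 times, and the primary ratio is 1.12 to 1.31.

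Statistical methods {20a} describes the CBF outcome as change from baseline to V1, which could suggest a two-visit fit. But it refits Eq. 1 and refers back to the sample size section, which says all visits.

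The joint scaling in the 15% case is disclosed; the complaint is only about what that case can show. Extending the point to MADRS would need a variance the article does not give.

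**Conclusion.** The concern holds as one of wrong error bars and lost efficiency. Under the plan's own variance assumptions and arm-coded Drug, Eq. 1 reports an SE for the primary contrast 1.15 to 1.40 times the true value at 25 per arm; under time-varying coding the range is about 1.0 to 1.3. The cost is an over-wide interval and up to about 8 percentage points of power (0.896 against 0.98). The contrast estimate is not biased, and the planned sample size stands under the base assumptions.

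The within-arm contrasts fare worse, and not always in the safe direction. The placebo SE is roughly 6.5 to 8 times too large under 3% retest variability, and the psilocybin SE is about 18% too small if the response repeats. The fixed-effect model selection in {20a} cannot repair any of this. The 15% sensitivity case does not show robustness to a smaller mean effect at unchanged variability.

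**What to change.** Use one of these for the primary contrast, and fix it before unblinding:
- V0 and V1 only, with arm-specific variances: for example a Welch-type comparison, or heteroscedasticity-robust SEs, on V1−V0 change adjusted for age and sex.
- An all-visit model with unstructured covariance, separate by arm and visit, and Satterthwaite or Kenward-Roger degrees of freedom.

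Dropping V2 while keeping one pooled variance would correct the between-arm SE but not the within-arm SEs.

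Define the coding of Drug. Keep Eq. 1 as a secondary all-visit analysis. Re-run the power simulation with the chosen model and state the assumed V1/V2 response correlation. In Sample size {14}, say that the 15% case leaves the standardised effect unchanged, and add the case with mean 15% and SD 23%.

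The cost is a different model call, a re-run simulation and a few more variance parameters, which take some degrees of freedom in a trial of 50. The added sensitivity figure, about 71% with arm-specific variances, falls below the 80% target and will look less favourable than the present one. No new data or visits are needed.

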### Recruitment {15}

As our participant recruitment will solely occur through referral by the multidisciplinary team within the participant’s circle of care at the Harquail Centre for Neuromodulation and the Mood and Anxiety Disorders Clinic at Sunnybrook Health Sciences Centre, particular strategies for participant enrolment will not be required to reach our target sample size.

## Assignment of interventions: allocation

### Sequence generation {16a}

Participants will be randomized with a computer-generated 1:1 randomized allocation into either the psilocybin or placebo group for dosing visit 1 by an independent external assistant using REDCap Randomization Module. Each participant will have an equal probability of being added to either group. Group sizes will be fixed, and study personnel will be blind to randomized allocation. A flowchart for participant randomization is provided [see Additional file 5]. All participants will receive open-label psilocybin at the second treatment visit.

### Concealment mechanism {16b}

The randomized 1:1 allocation sequence will be conducted using the Randomization Module in REDCap software. Each medication bottle label will contain a blinded, unique code that is associated with a specific treatment. Usona Institute will supply a master list containing the correspondence between the blinded, unique codes and their respective treatments. This list will be enclosed within an envelope and securely locked away, inaccessible to all study personnel.

### Implementation {16c}

Participants will be enrolled by the Qualified Investigator upon meeting inclusion criteria (see Table 1) and providing their informed consent. Each bottle of drug product (containing one capsule per bottle) will be labelled by Usona Institute with a tear-away portion denoting the bottle and subject ID to facilitate randomization. The study coordinator will assign a unique identifier to each participant and provide an independent external assistant with subject IDs, bottle IDs, and tear-away portions for randomization. Random assignment to the treatment or control group will be conducted using a computer-generated sequence using REDCap, ensuring equal allocation. The independent external assistant, without involvement from study personnel, will generate the allocation sequence and create a master list of tear-aways concealed in an opaque envelope. Subsequently, the study coordinator will label each bottle according to the randomly assigned subject-bottle ID list.

**Table 1 Tab1:** Inclusion and exclusion criteria

	**Inclusion criteria**
**Consent**	Must be able and voluntarily willing to provide written informed consent at the screening visit, with reconfirmed verbal consent provided at the beginning of each study visit
**Demographics**	
**Age**	Over 18 and under 65 years old
**Ability**	Able to complete all required assessment tools without assistance or alteration to the copyrighted assessments, as well as to comply with all required study visits
**Responsible Individual/Caregiver**	Must have a responsible individual/caregiver who is able to monitor the participant at home for 24 h after each treatment visit
